**Fig. 1 Fig1:**
[figure not shown]
Recruitment

**Fig. 2 Fig2:**
[figure not shown]
Participant timeline

**Fig. 3 Fig3:**
[figure not shown]
Schedule of enrollment, interventions, and assessment

### Randomization {16 a,b,c}

Randomization will take place just before the start of surgery by one of the researchers of the sponsor, who is present in the operating room during the entire procedure. A computerized program (CASTOR EDC) is used with a random block size of 2, 4, and 6. The randomization will be stratified by participating center. The assigned group (ACT or 5000 IU) is displayed on the computer, immediately after randomization. The researcher will inform the anesthesiologist which dose of heparin should be administered.

### Treatment details {11a}

#### ACT-guided heparinization

Heparin is given to reach an ACT of 200–220 s. At the start of the procedure, before any heparin is given, a baseline ACT measurement is performed. Three to 5 min before clamping of the aorta, 100 IU/kg bodyweight of heparin is administrated intravenously. If patients weigh more than 150 kg, a maximum heparin dose of 15,000 IU heparin is administered to prevent overdose.

Five minutes after administration of heparin, ACT measurement is performed. If the ACT is below 180 s, an additional dose of heparin of 60 IU/kg is administered. If the ACT is between 180 and 200 s, an additional dose of heparin of 30 IU/kg is administered, and if the ACT is 200 s or longer, no extra heparin is given.

Five minutes after every administration of heparin, the ACT is measured. If the ACT is 200 s or longer, the next ACT measurement is performed every 30 min, until the end of the procedure or until new heparin administration is required (because of ACT < 200 s). After each new dose of heparin, an ACT measurement is performed after 5 min and the above-described protocol of ACT measurements will be repeated. After re-establishing blood flow and removing all clamps, the ACT is measured. Depending on that ACT value near the end of the surgery, protamine is given to neutralize the effect of heparin.

If the ACT at closure is between 200 and 250 s, 2500 IU protamine should be administered. If the ACT is higher than 250 s, 5000 IU protamine should be administered, and if between 180 and 200 s, 1000 IU protamine. Five minutes after the administration of protamine, the ACT is measured. The ACT should preferably be below 180 s. If the ACT is still more than 200 s, protamine should be administered again using the above-mentioned protocol. When an additional dose of protamine is required, ACT measurement is performed 5 min after that administration.

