#### 5000 IU of heparin

A single dose of 5000 IU of heparin is given 3–5 min before clamping of the aorta. No ACT measurements are performed. Only on clarified indications, extra doses of heparin or protamine are permitted, at the discretion of the attending vascular surgeon. Deviations from the protocol will be clearly stated with reasoning in the operative report.

Patients with additional doses of heparin or protamine outside the protocol will not be excluded from the trial. Evaluation will be performed according to intention-to-treat analysis but also a per-protocol analysis will be performed and, if indicated, a sensitivity analysis.

In the intention-to-treat analysis, all patients who were randomised and meet the inclusion and exclusion criteria will be included.

A per-protocol analysis will be performed on the patients who fulfill the following:

ACT group:
Patients who received a starting dose of 100 IU/kg and reached an ACT ≥200 s within 30 min after cross clamping of the aorta with or without additional heparin dosages

and
2.Received extra dosage(s) of heparin in case ACT dropped below 200 s during cross clamping (noncompliance in case of restoration of arterial blood flow within 10 min is allowed)3.ACT at the end of surgery was <180 s with or without administration of protamine

5000 IU group:

The patient received a start dose of 5000 IU of heparin.

Patients will be excluded from the per-protocol analysis if:

ACT group:
Patients who did not receive a starting dose of heparin of 100 IU/kgPatients who did not reach an ACT > 200 s within 30 min after cross clamping of the aortaPatients who received extra heparin despite ACT > 200 s during cross clampingPatients who received protamine despite ACT < 180 after restoration of arterial blood flowPatients where the administered dose of heparin or protamine deviates from the directions in the protocol with more than 50% (upper or lower)

5000 IU group:
Patients who did not receive a starting dose of heparin 5000 IU

Patients will not be transferred to the other group.

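### An ACT-arm patient left at 180–200 s after protamine has followed the repeat-protamine rule, yet fails the per-protocol requirement of an end-of-surgery ACT below 180 s

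*Protocol article*

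**What the plan says.** All references are to the protocol article.

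- **Treatment details, ACT-guided heparinization, first protamine decision.** Once flow is restored and the clamps are off, the ACT is measured: "Depending on that ACT value near the end of the surgery, protamine is given to neutralize the effect of heparin". The lowest step of the schedule is "if between 180 and 200 s, 1000 IU protamine".
- **Same section, five minutes after protamine.** A value below 180 s is stated as a preference. The action rule is "If the ACT is still more than 200 s, protamine should be administered again using the above-mentioned protocol".
- **Treatment details, 5000 IU of heparin (where the per-protocol set is defined).** The third ACT-group condition is "ACT at the end of surgery was <180 s with or without administration of protamine". The separate list of per-protocol exclusions names protamine given at an ACT below 180 s and doses more than 50% away from the directions. It does not name an end ACT of 180 s or more. Control patients need only the 5000 IU starting dose.
- **Primary safety study parameter.** Non-inferiority for bleeding (11% margin) is established only if the confidence interval excludes the limit in both the per-protocol and the intention-to-treat analyses.
- **Heparin top-ups.** The dosing section describes ACT checks running "until the end of the procedure or until new heparin administration is required (because of ACT < 200 s", whereas the per-protocol definition ties top-ups to the clamp period: "Received extra dosage(s) of heparin in case ACT dropped below 200 s during cross clamping".

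**The concern.** A per-protocol set is meant to hold patients who were treated as the protocol directs. Here the dosing section and the per-protocol definition use different cut-offs for the same final reading, so following the first can mean failing the second. The two per-protocol lists also disagree: the patient is not included under one and not excluded under the other. Two analysts could build different sets from the same data.

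The per-protocol set is half of the decision on the primary safety endpoint. The criterion has no counterpart in the control arm, where no ACT is measured. It selects on residual anticoagulation at the end of surgery, which could be related to bleeding. Removing such patients from one arm gives up the protection of randomisation in the analysis that is supposed to guard against a falsely reassuring result.

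**Working it through.** The plan states no figure on this point, so the check is to apply each rule to the same ACT value.

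| ACT (s) | First reading after clamps are off | Reading 5 min after protamine | Per-protocol condition 3 if this is the final value |
|---|---|---|---|
| 170 | no protamine step | no repeat | met |
| 180 | 1000 IU | no repeat | **failed** |
| 190 | 1000 IU | no repeat | **failed** |
| 199 | 1000 IU | no repeat | **failed** |
| 200 | 2500 IU | no repeat | **failed** |
| 201 | 2500 IU | repeat | failed, but the rule still calls for action |

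(The schedule's steps meet at 200 s; the table puts 200 s in the upper step.)

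Every final post-protamine value from 180 to 200 s inclusive is consistent with the repeat rule and fails condition 3. Above 200 s there is no conflict, because a repeat is still due. Below 180 s there is none either.

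**Number affected.** The documents give no distribution of post-protamine ACT. With about 750/2 = 375 ACT-arm patients and an assumed 5–15% in the band:

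- 0.05 × 375 = 18.75, about 19 patients
- 0.15 × 375 = 56.25, about 56 patients

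**Possible shift in the per-protocol bleeding rate.** The sample size section expects 33% bleeding in the intervention arm. If a fraction f is dropped and those patients bleed at rate r, the rate among those retained is (0.33 − f·r)/(1 − f). With r = 50%, which is an assumption:

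- f = 5%: (0.33 − 0.025)/0.95 = 32.1%, a shift of 0.9 points
- f = 10%: (0.33 − 0.050)/0.90 = 31.1%, a shift of 1.9 points
- f = 15%: (0.33 − 0.075)/0.85 = 30.0%, a shift of 3.0 points

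If r = 33%, the shift is zero. If r is below 33%, it runs against the ACT arm.

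**Loss of numbers.** With expected rates of 32% and 33%, the distance to the 11% margin is 0.10. Power is Φ(0.10/SE − 1.96) at the one-sided 0.025 level given for the analysis, with SE = √(0.32·0.68/375 + 0.33·0.67/n) and n the ACT-arm number. For n = 375 this gives 83.2%; for 10% fewer (n = 337.5) it gives 81.2%. The selection matters more than the loss of size.

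**The case against.** **The two analyses protect each other.** Intention-to-treat keeps these patients and must also pass, so their removal cannot by itself produce a non-inferiority claim. This stands, and it limits the consequence to a weaker per-protocol check.

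**The direction of bias is not shown.** The Background cites two studies that found no relation between ACT and bleeding, and one that found more bleeding above 250 s, well outside this band. The endpoint also counts peroperative transfusion, part of which precedes the final ACT. This stands too: a shift favouring the ACT arm is plausible, not established.

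**Starting at 180 s but repeating only above 200 s can be deliberate.** It can. The two thresholds apply to different readings, the rule can be carried out as written, and the target below 180 s is only a preference. A reader might infer that the first and repeat rules are themselves in error and need one common threshold. The documents do not support that. The mismatch is with the per-protocol definition.

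**Heparin against protamine.** A reader might also infer that a reading such as 190 s late in surgery calls for both drugs, since "If the ACT is between 180 and 200 s, an additional dose of heparin of 30 IU/kg is administered" names no surgical phase and the ACT loop is worded to run to the end of the procedure. Read in order, the dosing section assigns the reading after clamp removal to protamine, and the per-protocol text confines top-ups to cross clamping. This is loose wording and does not establish opposing instructions or a safety hazard. The Discussion adds that a trained team member attends every procedure and performs all ACT measurements.

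**Conclusion.** The point holds as a conflict between the repeat-protamine rule and the third ACT-group per-protocol condition. For any final post-protamine ACT from 180 to 200 s, a patient treated as directed does not meet per-protocol inclusion, and the exclusion list leaves the case unaddressed. It would be too strong to call such patients off protocol: they miss one inclusion item and remain in the intention-to-treat set.

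The consequence is a less trustworthy per-protocol analysis of bleeding, because the criterion acts in one arm only and on a post-treatment value. The size is unknown. The 19 to 56 patients and the shift of 0.9 to 3.0 points against an 11-point margin rest entirely on the assumed 5–15% frequency and the assumed 50% bleeding rate among those dropped. The internal conflict itself needs no assumption. The wording on when heparin top-ups end is a minor clarification.

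**What to change.** 1. Reconcile the third ACT-group per-protocol condition with the repeat-protamine rule. Which threshold applies is for the sponsor to decide.
2. Make the inclusion and exclusion lists complementary, so that every ACT-arm patient falls clearly in or out.
3. Define per-protocol status in the ACT arm by whether the heparin or protamine instruction for each measured ACT was carried out, within the 50% tolerance already stated, and not by the ACT reached. If an analysis of patients who reached the target is still wanted, label it supplementary and keep it out of the non-inferiority decision.
4. As a clarification, reconcile the end point of the heparin loop in the dosing section with the cross-clamping limit in the per-protocol definition.

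The cost is a wording amendment and a short note to sites. ACT values and the amounts of heparin and protamine are already study parameters, and the existing 50% rule already requires each dose to be compared with its instruction. The article reports 90 of 750 patients included. The change should be made before any comparative bleeding data are seen by those who define the set, since a later redefinition would look data-driven.

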#### 5000 IU of heparin

A single dose of 5000 IU of heparin is given 3–5 min before clamping of the aorta. No ACT measurements are performed. Only on clarified indications, extra doses of heparin or protamine are permitted, at the discretion of the attending vascular surgeon. Deviations from the protocol will be clearly stated with reasoning in the operative report.

Patients with additional doses of heparin or protamine outside the protocol will not be excluded from the trial. Evaluation will be performed according to intention-to-treat analysis but also a per-protocol analysis will be performed and, if indicated, a sensitivity analysis.

In the intention-to-treat analysis, all patients who were randomised and meet the inclusion and exclusion criteria will be included.

A per-protocol analysis will be performed on the patients who fulfill the following:

ACT group:
Patients who received a starting dose of 100 IU/kg and reached an ACT ≥200 s within 30 min after cross clamping of the aorta with or without additional heparin dosages

and
2.Received extra dosage(s) of heparin in case ACT dropped below 200 s during cross clamping (noncompliance in case of restoration of arterial blood flow within 10 min is allowed)3.ACT at the end of surgery was <180 s with or without administration of protamine

5000 IU group:

The patient received a start dose of 5000 IU of heparin.

Patients will be excluded from the per-protocol analysis if:

ACT group:
Patients who did not receive a starting dose of heparin of 100 IU/kgPatients who did not reach an ACT > 200 s within 30 min after cross clamping of the aortaPatients who received extra heparin despite ACT > 200 s during cross clampingPatients who received protamine despite ACT < 180 after restoration of arterial blood flowPatients where the administered dose of heparin or protamine deviates from the directions in the protocol with more than 50% (upper or lower)

5000 IU group:
Patients who did not receive a starting dose of heparin 5000 IU

Patients will not be transferred to the other group.

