### Study design {8}

The ACTION-1 trial is a multicenter RCT designed to compare the outcomes of ACT-guided heparinization to a standardized bolus of 5000 IU of heparin, during open AAA repair.

Patients undergoing open AAA repair, meeting eligibility criteria, will be included in the trial after giving written informed consent.

The following Dutch vascular centers (academic and large community training hospitals){9} are currently, or in upcoming months, participating in the ACTION-1 trial: Dijklander Ziekenhuis Hoorn, Amsterdam UMC location VUmc, Amsterdam UMC location AMC, Rijnstate Ziekenhuis Arnhem, Elisabeth-TweeSteden Ziekenhuis Tilburg, Isala Ziekenhuizen location Zwolle, Medisch Spectrum Twente Enschede, Maasstad Ziekenhuis Rotterdam, Groene Hart Ziekenhuis Gouda, St. Antonius Nieuwegein, Alrijne Ziekenhuis Leiderdorp, LUMC Leiden, Amphia Ziekenhuis Breda, Haaglanden MC Den Haag, Gelre Ziekenhuizen Apeldoorn, Slingeland Ziekenhuis Doetinchem, Catharina Ziekenhuis Eindhoven, Zorggroep Twente location Almelo, UMCG Groningen.

Also, the University Heart Center Hamburg is in preparation for intended participation. A website solely for the ACTION-1 study has been developed: ACTION-1.nl. All participating hospitals, inclusion, and information for patients (including lay video) are depicted on this website {9} (Appendix).

The study will be single blinded: only the patient will be fully blinded. Furthermore, the Independent Central Adjudication Committee (ICAC) and the data analysts will be blinded for the intervention {17a}. Blinding will follow all legal demands for unblinding in case of patient safety, as deemed as such by attending medical personnel {17b}. Also, the Data Safety Monitoring Board (DSMB) can decide to unblind.

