### Inclusion criteria {10}

Inclusion criteria are able to speak and read in the local language of the trial hospital; patients older than 18 years scheduled for elective, open repair of an iliac or abdominal aortic aneurysm distal of the SMA (DSAA segment C); implantation of a tube or bifurcation prosthesis; trans-abdominal or retroperitoneal surgical approach of aneurysm; and able and willing to provide written informed consent.

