### Exclusion criteria {10}

Exclusion criteria are not able to provide written informed consent; previous open or endovascular intervention on the abdominal aorta (previous surgery on other parts of the aorta or iliac arteries is not an exclusion criterion); history of coagulation disorders, heparin-induced thrombocytopenia (HIT), allergy for heparin or thrombocyte pathology; impaired renal function with EGFR below 30 ml/min; acute open AAA surgery; hybrid interventions; connective tissue disorders; dual anti-platelet therapy, which cannot be discontinued; life expectancy less than 2 years; inflammatory, mycotic, or infected aneurysms; and allergy for protamine or fish protein.

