### Statistical analysis {20 a,b,c}

Descriptive statistics of continuous variables will be presented as means with standard deviations (SD) or medians with inter-quartile ranges (IQR) depending on the distribution of the data.

Categorical data will be presented as proportions and numbers. The statistical efficacy analysis will be conducted according to the intention-to-treat principle. A separate per-protocol analysis will be performed additionally as a sensitivity analysis. All analyses will be performed with the latest version of the Statistical Package for Social Sciences (SPSS, SPSS Inc., Armonk, NY, USA).

The analysis of primary efficacy and safety outcomes will be performed on an intention-to-treat basis and in a hierarchical fashion. If the statistical analysis shows that there is a statistically significant difference in the primary efficacy endpoint, a statistical analysis of the primary safety study parameter will be performed. If there is no significant difference between study groups in primary efficacy endpoint, assessment of primary safety endpoint will be considered exploratory. Subjects with missing data will be excluded per analysis.

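### The intention-to-treat set is limited to randomised patients who meet the eligibility criteria, with no rule that eligibility be judged on pre-randomisation facts or blind to arm

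*Protocol article*

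**What the plan says.** The definition of the analysis set stands in the protocol article under Treatment details {11a}, subsection 5000 IU of heparin. For the intention-to-treat analysis, "all patients who were randomised and meet the inclusion and exclusion criteria will be included". The same subsection keeps patients who had heparin or protamine outside the protocol, and does not move patients between groups.

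Statistical analysis {20 a,b,c} then states: "The analysis of primary efficacy and safety outcomes will be performed on an intention-to-treat basis and in a hierarchical fashion". It adds one rule for missing data: "Subjects with missing data will be excluded per analysis".

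On who knows the allocation, Study design {8} says "The study will be single blinded: only the patient will be fully blinded", and that "the Independent Central Adjudication Committee (ICAC) and the data analysts will be blinded for the intervention". Under Randomization {16 a,b,c}, patients are randomised just before surgery starts. "The assigned group (ACT or 5000 IU) is displayed on the computer, immediately after randomization", and the researcher in the operating room tells the anaesthesiologist which heparin dose applies.

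The inclusion criteria contain "implantation of a tube or bifurcation prosthesis". The exclusion criteria contain inflamed or infected aneurysms and "hybrid interventions".

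**The concern.** An intention-to-treat analysis is protected because membership is fixed at randomisation. Here membership also depends on a judgement about eligibility, and the text does not say when that judgement is made, by whom, or on what facts. Most criteria are settled in the clinic. A few can be confirmed, or turn out differently, once the abdomen is open, when the team already knows the arm. Primary endpoint events can occur in the same operation, since the composite includes peroperative thrombosis that needs further action.

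If removals then differ between arms in a way related to outcome, the comparison is no longer the randomised one. Both the superiority test on TEC and mortality and the non-inferiority test on bleeding would be affected, because both use this set. The label would also mislead readers, who will take it to mean all randomised patients.

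**Working it through.** **1. The plan's own figure.** Inputs from Sample size calculation {14}: 19% versus 11%, two-sided alpha 5%, power 80%, continuity-corrected chi-square, 10% dropout.

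- Uncorrected: n = [1.960·√(2·0.15·0.85) + 0.842·√(0.19·0.81 + 0.11·0.89)]² / 0.08² = 311.5, so 312 per group.
- Corrected: (n/4)·[1 + √(1 + 4/(n·0.08))]² = 336.1, so 337 per group.
- With dropout: 337/0.9 = 374.4, so 375 per arm and 750 in total.

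The stated 337 and 750 reproduce. The sample size is not in question; the analysis set is.

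**2. Is there a safeguard elsewhere in the article?**

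| Possible safeguard | What the article provides |
|---|---|
| Eligibility fixed on pre-randomisation facts | Not stated |
| Eligibility judged blind to arm | Not stated. The blinded adjudication committee reviews the complication parts of the case report form, not eligibility |
| Treating team blind | No |
| Off-protocol dosing kept in | Yes, but this does not cover patients found ineligible |

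**3. How few selective removals matter in a borderline result (assumed counts).** Pooled two-proportion test, z = (p₁ − p₂)/√[p(1 − p)(1/n₁ + 1/n₂)].

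- 64/337 versus 46/337: 19.0% versus 13.6%, z = 0.0534/0.02847 = 1.88, p = 0.061.
- Four ACT-arm patients with events removed, 64/337 versus 42/333: 19.0% versus 12.6%, z = 0.0638/0.0282 = 2.26, p = 0.024.
- With the continuity correction the two p-values are 0.076 and 0.031, so the change of verdict persists.

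**4. Range of the distortion if there is no true effect (assumed).** Take 19% in both arms, 375 per arm, and removals from the ACT arm only. If a fraction f is removed with event risk r, the remaining rate is (0.19 − f·r)/(1 − f).

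| Removed from ACT arm | Risk of those removed | Spurious benefit (points) | Type I error |
|---|---|---|---|
| any | average (19%) | 0 | 5.0% |
| 2% (7–8 patients) | 2 to 3 times average | 0.4 to 0.8 | 5.2 to 5.8% |
| 5% (about 19) | 2 to 3 times average | 1.0 to 2.0 | 6.4 to 10.8% |
| 10% (about 38) | 2 to 3 times average | 2.1 to 4.2 | 11 to 32% |

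The article gives no ineligibility rate, so no row can be called the expected one.

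**5. Missing outcomes (assumed).** Take 64 versus 37 events of 337 observed (p = 0.004), 38 more patients missing per arm, and missing controls at 19%. With missing ACT patients at 30%, 35% and 39%, p is 0.023, 0.038 and 0.056. The planned effect is lost only near 39%, about 3.5 times the observed ACT rate of 11%.

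**The case against.** The strongest reply is that few patients can be affected. Consent, renal function, coagulation history, allergy, earlier aortic intervention and life expectancy are all known beforehand, and randomising just before surgery leaves a short window. Adjudicators and analysts are blinded. Off-protocol dosing removes nobody from the intention-to-treat set. Non-inferiority for bleeding must hold in the per-protocol set as well, so it does not rest on this set alone. All of this stands and limits the likely size, but none of it governs how eligibility is judged after allocation is known.

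Four stronger readings are tempting and not supported.

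- A reader might infer that an intraoperative thrombus treated endovascularly would turn a case into an excluded hybrid. The criteria concern scheduled open repair, and "hybrid interventions" reads naturally as the planned procedure. The endpoint sections count peroperative thrombus needing action as a primary event.
- A reader might infer that the missing-data rule drops a patient with an observed TEC whose follow-up is incomplete. Exclusion per analysis can equally mean only patients whose status for that analysis is unknown. The wording is ambiguous, no more.
- A reader might set the 10% dropout allowance (75 of 750 patients) against the planned difference of 27 events (64 minus 37). The allowance is a sample-size margin, not a forecast of missing outcomes, and the comparison does not measure bias. Missingness should be low, since the endpoint is 30-day or in-hospital and the data come from patient files.
- A reader might contrast the rule with the multiple imputation planned for the economic evaluation. That analysis relies on questionnaires up to 26 weeks and faces a different problem.

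**Conclusion.** The point holds as a defect in a stated rule. The set called intention-to-treat is a modified set from which randomised patients can be removed after the team knows the arm, with no stated condition on the facts used or on blinding. Both primary tests rest on it.

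The document does not show that bias will occur, and its size cannot be derived. It is zero if removals are unrelated to outcome and small if they are rare. The change from p = 0.061 to p = 0.024 assumes a borderline result and four removals, all with events and all from one arm; it shows sensitivity, not expectation. The missing-data rule is a secondary, ambiguous point, and the planned effect withstands fairly severe assumptions about missing outcomes. Severity: should be fixed.

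**What to change.** Define the intention-to-treat set as all randomised patients, analysed in the allocated arm whatever is later found about eligibility or prosthesis type. If an analysis restricted to eligible patients is wanted, make it a sensitivity analysis, with eligibility based on pre-randomisation facts and judged by someone blind to arm and outcome.

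For the primary endpoints, replace "Subjects with missing data will be excluded per analysis" with a rule that any observed TEC, death or bleeding event counts as an event in its endpoint even if follow-up is incomplete. Add a sensitivity analysis for outcomes that remain missing.

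The cost is a few sentences and a little extra analysis, settled before unblinding. Sample size, conduct and treatment do not change. The downside is that a few ineligible patients may dilute the effect slightly. Against that, if all 375 per arm are analysed, power for 19% versus 11% is 86.8%, compared with 83.0% at 337 per arm (both by the uncorrected formula).
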